### Criteria for stopping the intervention

The intervention will be paused for significant hemodynamic changes, defined as a sustained (>15 min) increase or decrease in mean arterial pressure (MAP) of more than 30% from baseline or the last recorded stable value and is clinically symptomatic. It will be stopped if spinal cord perfusion pressure (SCPP) decreases to <65 mmHg for more than 15 min despite standard clinical management, including appropriate vasopressor titration. The intervention will also be paused for severe hemodynamic instability, such as persistent bradycardia, hypotension, or hypertension despite appropriate medical management, or for signs of autonomic dysreflexia, including sudden severe headache, flushing and profuse sweating above the level of injury, hypertension, bradycardia, anxiety, blurred vision, or nausea. Any serious adverse event deemed related to the intervention by the Principal Investigator or the safety monitor, or any unanticipated adverse device effect, will result in immediate suspension of the intervention pending further evaluation. If the patient experiences clinical deterioration that precludes participation (e.g., severe sepsis or coma), the intervention will be paused and reassessed. If the intervention is permanently discontinued, observational data collection will continue without further stimulation or sham trials until hospital discharge.

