### Outcomes

Table 1 lists all trial outcome measures and the corresponding abbreviated statistical analysis plan.

**Table 1 tab1:** A list of outcome measures and the corresponding analysis plan.

Outcome measure	Description	Statistical analysis
Primary outcomes (safety)—Phase 1 and 2		
1. Incidence of adverse events (# of observed events/sessions)	Hemodynamic instability Skin irritation Patient condition deterioration Unanticipated adverse events	Data type: Count Data Statistical Test: Fisher’s Exact Test
Primary outcomes (efficacy)—Phase 2		
1. ISNCSCI lower motor scores	Immediate change in scores with acute tSCS Change in scores from baseline to post tSCS	Data Type: Integer Statistical Test: Repeated Measures Analysis of Variance
Secondary outcomes (efficacy)—Phase 1 and 2		
1 ISNCSCI sensory + motor scores	Change in scores from baseline to 7DPI or discharge	Data Type: Integer Statistical Test: Repeated Measures Analysis of Variance
2. Spinally motor evoked potentials (MEPs)	MEP present/elicited (binary measure) (within subject) # of muscles with elicitable MEP	Data Type(s): Binary, Count Statistical Tests: Chi-Square, Fisher’s Exact Test
3. Electromyography (EMG) amplitude	Change in EMG amplitude in the presence of tSCS vs. no stimulation (within subject) Change in number of muscles with EMG output	Data Type(s): Continuous, Count Statistical Tests: Repeated Measures Analysis of Variance, Fisher’s Exact Test
Secondary outcomes (biomarker discovery)—Phase 1 and 2		
1. Neuronal (UCH-L1) and glial cell (GFAP) injury markers in blood	Changes in protein levels from baseline to post tSCS vs. sham	Data Type: Continuous Statistical Tests: Repeated Measures Analysis of Variance
2. CSF proteomics	Changes in protein levels from baseline to post tSCS vs. sham	Data Type: Continuous Statistical Tests: Non-linear Principal Components Analysis, followed by RM-ANOVA on PC scores
Secondary outcomes (patient-reported outcomes)—Phase 1 and 2		
3a. Incidence of neuropathic pain at 6-month follow-up 3b. Severity of neuropathic pain at 6-months follow-up	Modified DN4 questionnaire will be used to assess neuropathic pain at 6-months follow-up in tSCS vs. sham individuals (vs. historical TRACK-SCI participants)	Data Type: Integer, or Binarized at ≤ indicating neuropathic pain Statistical Test: Independent group Student’s *t*-test, or Chi-square

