### Harms

Potential harms associated with study participation include risks related to tSCS, biospecimen collection, and data privacy. Adverse events related to tSCS may include autonomic changes such as autonomic dysreflexia, manifested by blood pressure fluctuations, sweating, or headache, as well as skin irritation at electrode sites. Autonomic dysreflexia is less common in the acute phase of SCI but will be monitored closely. Although electrical stimulation in the acute phase of SCI could theoretically impair neurological recovery, this has not been observed in prior studies of chronic SCI. Risks associated with blood collection include transient pain, bruising, redness or swelling at the venipuncture site, infection, and rare episodes of fainting; blood will be drawn from existing intravenous lines whenever possible to minimize these risks. Cerebrospinal fluid sampling will be performed via an existing lumbar drain, accessing the drain carries a potential risk of infection, which will be mitigated through sterile technique. Risks related to privacy and confidentiality will be minimized through de-identification of data and biospecimens and secure storage procedures. Harms will be assessed systematically throughout the trial. Participants will be continuously monitored in the Neurointensive Care Unit, where neurological, cardiovascular, hematopoietic, abdominal, pulmonary, infectious, wound-related, and laboratory complications are routinely assessed as part of standard clinical care for acute spinal cord injury. Continuous telemetry and neurological examinations will be performed per standard of care. Vital signs will be recorded during tSCS sessions, along with surface electromyography recordings. The study team will document all vital signs and any vasoactive medications or infusions administered during stimulation sessions. All adverse events will be recorded by the study team and reviewed by the PI and the safety monitor. Events will be categorized by severity (mild, moderate, or severe) and assessed for their relationship to study participation (unrelated, possibly related, probably related, or definitely related). Serious adverse events and unanticipated adverse device effects will be reported in accordance with UCSF Institutional Review Board and sponsor requirements. Predefined stopping criteria include clinically significant hemodynamic instability, autonomic dysreflexia, deterioration in clinical status, and any serious adverse event judged to be related to the intervention.

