We will measure glial fibrillary acidic protein (GFAP) and ubiquitin C-terminal hydrolase L1 (UCH-L1) in blood and CSF on the first day of stimulation prior to the first stimulation session (~72 h after injury). We will also measure these in blood on the final day of stimulation (treatment #5) or discharge, after last treatment, whichever is earlier. We will measure these in CSF on the final treatment before discharge, or before the lumbar drain is taken out if this happens before discharge, after treatment. GFAP and UCH-L1 will be assayed at ZSFG on the Abbott Alinity I Immunoassay system. At those same 2 time points we will also conduct a global discovery proteomic assay on both plasma and CSF. We will use the commercially available high-throughput protein biomarker discovery platform based on Olink’s Proximity Extension Assay (PEA), which reliably measures >5,400 proteins using <1 mL of biofluid.

At 6-month follow-up visit, participants will be asked about any adverse experiences and ISCNSCI with EMG assessment will be performed. We will also administer a modified DN4 and SCI Pain Basic Data Set questionnaire to assess presence of neuropathic or any other pain, the Spinal Cord Independence Measure (SCIM) to assess functional independence and Neuro-QoL (Lower Extremity function (Mobility) Short Form and Positive Affect and Well Being Short Form) to assess quality of life. See Figure 1 for a timeline of all study assessments.

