### Analysis of primary and secondary efficacy outcome measures

For all participants, the primary outcome measure(s) will be: incidence of adverse events (number) for Phase 1 and 2 and change in ISNCSCI lower motor score over time for Phase 2. Secondary outcomes in both phases will be: ISNCSCI sensory scores, AIS grade, peak EMG amplitude, and mean EMG amplitude. For Phase I, change scores will be measured between baseline and post-trial, and in Phase II each measure will be taken across 5 trials. For all repeated measures analyses, we will use a factorial within-subjects repeated-measures analysis of variance (RM-ANOVA) to assess statistically significant change over time. This approach will allow us within a single statistical test to assess (1) the overall between-subjects effect of stimulation to determine the group differences between the stimulation and control groups, (2) the difference in changes over time between groups, and (3) the within-subjects effect of stimulation over trials, to determine the extent to which each individual changes over time. The RM-ANOVA procedure will be run for each outcome measure.

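### The primary safety outcome is given as events per session with no event window and elsewhere as a plain number, while adverse events are collected well beyond the sessions

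*Protocol article*

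**What the plan says.** The outcome is worded in two ways in the protocol article:

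- Outcomes, Table 1, primary safety outcome for Phases 1 and 2: "Incidence of adverse events (# of observed events/sessions", with the analysis entry "Data type: Count Data Statistical Test: Fisher’s Exact Test". The listed components are "Hemodynamic instability Skin irritation Patient condition deterioration Unanticipated adverse events". No event window is stated.
- Analysis of primary and secondary efficacy outcome measures: "incidence of adverse events (number) for Phase 1 and 2". There is no session denominator.

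The collection of adverse events is wide:

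- Harms: "Harms will be assessed systematically throughout the trial", and "All adverse events will be recorded by the study team and reviewed by the PI and the safety monitor". Relatedness is graded and includes an unrelated category, so unrelated events are recorded too.
- Criteria for stopping the intervention: after permanent discontinuation, "observational data collection will continue without further stimulation or sham trials until hospital discharge".
- Data collection methods, 6-month visit: "participants will be asked about any adverse experiences".

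Sessions are few and short: one of 60 minutes in Phase 1, and one a day for five days in Phase 2.

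**The concern.** A rate is interpretable when its numerator and denominator refer to the same exposure. Here the denominator is a handful of one-hour sessions, and the only stated collection period for events is the whole trial. Two of the four components, deterioration and unanticipated events, are not naturally confined to an hour of stimulation.

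If all recorded events go into the numerator, a participant who stops after session 1 goes on adding events until discharge while adding nothing further to the denominator. The article foresees fewer than five sessions: the stopping criteria allow it, and the final biomarker sample is timed to the fifth treatment or discharge, whichever is earlier. Some grounds for pausing or stopping also overlap the outcome's own components, so an event can both enter the numerator and shrink the denominator.

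Safety is the main purpose of Phase 1 and a primary outcome in Phase 2. Two analysts following the article could report different headline safety figures from the same data.

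**Working it through.** The article states no event rate, power or sample size for safety, so there is no safety figure to reproduce. The event counts below are assumptions.

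**Planned sessions** (Trial design; Intervention and comparator)
- Phase 1: 5 participants × 1 = 5.
- Phase 2: 5 participants × 5 = 25 per arm.

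**Share of observation time in sessions** = session hours / observed hours, starting at 72 h after injury
- To day 7: 168 − 72 = 96 h. Phase 1: 1/96 = 1.0%. Phase 2: 5/96 = 5.2%.
- To day 11, using the average stay quoted in the Introduction: 264 − 72 = 192 h. Phase 1: 1/192 = 0.5%. Phase 2: 5/192 = 2.6%.
- The 11 days is a background average, not a trial window, and it counts from admission rather than injury. These are shares of time, not of events.

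**If all recorded events are counted: Phase 1 against Phase 2.** Rate = events per participant / sessions per participant.

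| Events per participant (assumed) | Phase 1 | Phase 2 | Ratio |
|---|---|---|---|
| 0.5 | 0.5 | 0.1 | 5 |
| 1 | 1.0 | 0.2 | 5 |
| 2 | 2.0 | 0.4 | 5 |
| 4 | 4.0 | 0.8 | 5 |

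The ratio is 5/1 whatever the event rate.

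**If all recorded events are counted: active against sham in Phase 2.** At equal event counts the rate ratio is 25 / active sessions delivered, with sham complete.
- Full delivery: 25/25 = 1.00.
- One active participant stops after session 2: 25/22 = 1.14.
- One stops after session 1: 25/21 = 1.19.
- Two stop after session 1: 25/17 = 1.47.

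The session-level Fisher test moves in the same way. With 10 events in each arm and 25 sham sessions, the two-sided p is 0.56 with 20 active sessions, 0.19 with 15 and 0.002 with 10. The last is an extreme case, shown for direction only.

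**Harm still moves the rate.** Take 2 background events per participant and 0.2 extra events per active session, with full delivery. Active is (2 + 5 × 0.2)/5 = 0.6 per session, and sham is 2/5 = 0.4.

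**When the table fails.** A 2×2 table of sessions with and without an event, filled from event counts, needs sessions − events ≥ 0. That breaks above one event per participant in Phase 1, and above five per participant in a Phase 2 arm with full delivery (fewer if sessions are missed).

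**If only events at sessions are counted.** Numerator and denominator match. Harms arising after a session, up to discharge or 6 months, then fall outside the primary outcome, although the Harms section itself raises a theoretical effect on neurological recovery.

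**With participants as the denominator.** The same events per participant give the same figure in both phases (ratio 1.0 instead of 5), and missed sessions do not change it. Fisher's exact test on participants, 5 v 5, is valid but coarse: 4/5 v 0/5 gives p = 0.048, and 3/5 v 0/5 gives p = 0.167.

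**The case against.** A reader might infer that the plan does divide stay-long and 6-month events by sessions, and that the rate therefore reflects sessions delivered rather than harm. The article does not support that. The Harms and Data collection sections say what is collected; no sentence says that all of it enters this numerator. A session-bound reading is open: Trial design and the Figure 1 caption describe Phase 1 as assessing the safety of one 60-minute application, and vital signs and vasoactive drugs are documented during sessions. The rate also responds to harm, as the 0.6 v 0.4 example shows.

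Other points for the plan also stand:
- With full delivery, both Phase 2 arms have 25 sessions and the denominator cancels in the only randomized comparison.
- No comparison of Phase 1 and Phase 2 rates is planned, and the step to Phase 2 rests on a qualitative review. The five-fold gap therefore distorts the reported figures rather than a planned test.
- The stopping criteria are themselves adverse clinical events, so more stopping on active treatment would partly be harm.
- Table 1 is an abbreviated plan, and a full protocol may define the event window.

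The last point does not dispose of the matter. The article does state a ratio and a test, and its own analysis section states the outcome differently. That inconsistency is in the text as published, and each reading of the ratio leaves a problem: a mismatch of time under one, later harms left out under the other.

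**Conclusion.** The point holds as a definition that is not fixed and is inconsistent between two sections; it is not a demonstrated mismatch. If all recorded events are counted, the per-session figure is five times higher in Phase 1 than in Phase 2 at equal events per participant, early stopping by one or two active participants shifts the active v sham ratio by 14% to 47% at equal event counts, and events can exceed sessions so that the stated test has no table. These sizes rest on assumed stopping patterns and on event counts that do not depend on sessions received. With full delivery the Phase 2 comparison is unaffected. If only session events are counted, the ratio is coherent but narrower than the harms the article sets out to assess. The definition should be corrected before safety data are summarized. It does not invalidate the design.

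**What to change.** Reconcile Table 1 and the analysis section so that both name the same measures, each with its own window:

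1. Main measure: participants with at least one adverse event from the first session to discharge, and separately to 6 months, over participants treated. In Phase 2, apply Fisher's exact test to participants. Do not divide this measure by sessions.
2. Descriptive measure: events with onset in a stated session window (for example, from electrode placement to a fixed time after the session ends) over sessions started.

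The cost is wording in two places, an onset time for each event and two safety tables instead of one. No visits are added. With five per arm the participant-level test will detect only very large differences, so the counts should be read descriptively alongside it.

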**Methods:**

STEP-RAISE is a Phase 1/2 prospective clinical trial evaluating the safety and preliminary efficacy of tSCS in acute moderate-to-severe traumatic SCI. Electrical current will be delivered to the lumbosacral spinal cord using the investigational ARC-Ex device (ONWARD Medical) via surface electrodes over the thoracolumbar region. Phase 2 is a randomized, triple-blinded, placebo-controlled trial designed to assess treatment effects. Safety outcomes include hemodynamics, spinal cord perfusion pressure, and skin reactions. Efficacy will be assessed using the International Standards for Neurological Classification of Spinal Cord Injury (ISNCSCI) examination with electromyography at baseline, during stimulation, and at 6-month follow-up. Biomarkers include neuronal (UCH-L1) and glial (GFAP) markers and exploratory proteomics in blood and cerebrospinal fluid collected prior to stimulation and at discharge.

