For ISNCSCI and neurophysiological assessment, the participant will be instrumented with 10 surface electromyography recording electrodes (Delsys, Inc), placed bilaterally over the lower extremity muscles: Rectus Femoris (RF), Biceps Femoris (BF), Medial Gastrocnemius (MG), Tibialis Anterior (TA), Extensor Hallucis Longus (EHL). Stimulating electrodes will be placed on the skin over the low thoracic, lumbar spine and the grounding electrodes will be placed over the iliac crest bilaterally. The stimulation will be delivered as single, 1-ms monophasic square-wave pulses every 6 s while patient is lying in supine. Using 2-mA increments, the stimulation intensity will be increased from 2 to 100 mA or if the participant requests to stop stimulation. Three stimuli will be delivered at each intensity. The stimulation will be delivered using an experimental Neo-Stim 5 (Cosyma, LTD) transcutaneous spinal cord stimulator, as ARC-Ex currently does not support single-pulse tSCS paradigm required to evoked discrete motor responses. Neurophysiological outcome measures will include the presence or absence of elicitable motor evoked potentials (MEPs) and the number of muscles demonstrating elicitable responses (Table 1). The neurophysiological assessment will be performed at baseline twice (before and right after the first 60 min of continuous tSCS) and at 7 days post-SCI (or at hospital discharge whichever is earlier) if the standard of care continuous vital signs monitoring is still ongoing. Frequent vital signs will be captured during tSCS for analysis and will be monitored continuously as per standard of care.

When available, clinically acquired MRI data and intraoperative MEPs obtained as part of standard care will be reviewed. MRI severity will be characterized using the Brain and Spinal Injury Center (BASIC) score and used as an exploratory descriptor of injury severity and natural recovery potential (Talbott et al., 2015; Dhall et al., 2018).

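### Hemodynamics and SCPP are named as safety outcomes and vasoactive drugs are recorded, but Table 1 reduces them to an undefined "Hemodynamic instability" count, and no analysis of MAP, SCPP, heart rate or vasopressor requirement is given

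*Protocol article*

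**What the plan says.** The abstract of the protocol article states: "Safety outcomes include hemodynamics, spinal cord perfusion pressure, and skin reactions". Under Harms: "The study team will document all vital signs and any vasoactive medications or infusions administered during stimulation sessions". Under Data collection methods: "Frequent vital signs will be captured during tSCS for analysis".

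The Outcomes section opens with "Table 1 lists all trial outcome measures and the corresponding abbreviated statistical analysis plan". The primary safety row for Phases 1 and 2 is "Incidence of adverse events (# of observed events/sessions", described as "Hemodynamic instability Skin irritation Patient condition deterioration Unanticipated adverse events", with the analysis entry "Data type: Count Data Statistical Test: Fisher’s Exact Test". Table 1 has no other hemodynamic entry and does not define the one it has.

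The only hemodynamic thresholds are under Criteria for stopping the intervention. There are four limbs:
- a MAP change of more than 30% that lasts over 15 min and is symptomatic;
- an SCPP limb: "It will be stopped if spinal cord perfusion pressure (SCPP) decreases to <65 mmHg for more than 15 min despite standard clinical management";
- severe instability that persists despite medical management;
- signs of autonomic dysreflexia.

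The section on primary and secondary efficacy analyses names adverse event incidence as the safety outcome. The later sections on patient-reported outcomes, biomarkers and the interim review add no MAP, SCPP, heart rate or vasopressor analysis.

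**The concern.** Safety is the first objective, and blood pressure fluctuation is among the first stimulation-related harms that the Harms section lists. The trial collects data that could show such an effect, but the stated outcome uses them only through a yes/no judgement with no definition.

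Two things follow. A count in 5 v 5 participants can separate the arms only if the difference is near total. And standard ICU care continues during the trial, so a fall in pressure may be treated as it happens. The recorded pressure then looks normal unless it is read with the change in vasopressor requirement, and no stated analysis does that. A real hemodynamic effect of stimulation could therefore be absent from the reported safety result, and from the qualitative, event-based Phase 1 review that precedes Phase 2.

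**Working it through.** The article gives no power, event rate or sample size for the safety outcome, so there is no figure to reproduce. The check has three parts.

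**1. The sections side by side**

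| Measure | Named as a safety outcome (abstract) | Recorded in sessions | Row in Table 1 | Analysis stated |
|---|---|---|---|---|
| MAP, heart rate | yes, as hemodynamics | yes, as vital signs | only as undefined instability | no |
| SCPP | yes | implied by the stop rule, not stated | none | no |
| Vasoactive drugs | no | yes | none | no |

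The abstract and the table that is said to list all outcomes therefore disagree.

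**2. What the count can show**

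Inputs: 5 active and 5 sham participants (Trial design), Fisher's exact test (Table 1). Assumptions: each participant is scored as any event or none, and the arms come out at 5 each.

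The two-sided p-value for a v b participants is twice the hypergeometric tail, since the arms are equal:
- 3 v 0: 2 × C(5,3)/C(10,3) = 2 × 10/120 = 0.167
- 4 v 0: 2 × C(5,4)/C(10,4) = 2 × 5/210 = 0.048
- 5 v 0: 2 × 1/C(10,5) = 2/252 = 0.008
- 4 v 1: 2 × (25 + 1)/252 = 0.206
- 5 v 1: 2 × C(5,1)/C(10,6) = 2 × 5/210 = 0.048
- 5 v 2: 2 × C(5,2)/C(10,7) = 2 × 10/120 = 0.167

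Only 4 v 0, 5 v 0 and 5 v 1 reach p≤0.05 in the harmful direction.

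The outcome is worded per session. With 5 sessions each, that is 25 v 25, treated as independent although sessions cluster within participants. Then 5 v 0 gives p = 0.0502 and 6 v 0 gives p = 0.022.

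Zero events bounds little. The one-sided 95% upper limit is 1 − 0.05^(1/n), which is 45% for n = 5 participants.

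**3. Illustration of uncounted events (assumed rates, not document figures)**

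Suppose 60% or 80% of active and 10% of sham participants have a hemodynamic event, and a share s of these is corrected and not counted. The counted rates are then 0.6(1 − s) or 0.8(1 − s), and 0.1(1 − s). Exact binomial enumeration of the Fisher rejection region gives:

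| s | Power, 60% active | Power, 80% active | Chance of zero counted active events (60%, 80%) |
|---|---|---|---|
| 0 | 22% | 54% | 1%, under 0.1% |
| 0.5 | 2% | 7% | 17%, 8% |
| 0.8 | 0.1% | 0.3% | 53%, 42% |

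For example, with 60% and s = 0.8 the counted rate is 0.12, and (1 − 0.12)^5 = 0.53.

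A separate comparison shows what a count loses against a measured change. Assume normal participant-mean changes and an event cut-off 1 to 2 SD beyond the sham mean. For a true shift of 1.5 SD, power is 55% on the continuous change (t test, 8 df) and 3–28% on the count. For 2.0 SD it is 79% and 17–51%. This measures the general cost of dichotomising. It does not measure vasopressor masking, which would also shrink the continuous pressure shift. That is why the drug change has to be read with the pressure.

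**The case against.** A reader might infer that only events persisting despite vasopressors are counted, so that any corrected effect is reported as no harm. The article does not support this. The thresholds sit under the stopping criteria, and nothing makes them the definition of the Table 1 item. The MAP and dysreflexia limbs carry no condition that treatment must first have failed. The Harms section says that all adverse events are recorded and graded from mild to severe, and it lists blood pressure fluctuation as a possible manifestation with no threshold. Nor is vasopressor use named as a safety outcome, or SCPP stated to be recorded in every session. All of this stands. It turns a certain loss into a possible one.

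The second objection is that Table 1 calls its analysis plan abbreviated and that vital signs are said to be captured for analysis, so a full SAP may supply the method. That holds for summary windows, derivations and models. It does not cover the outcome list, which the article presents as complete and which disagrees with its own abstract. Recording all adverse events does not settle the matter either, since nothing says whether a corrected pressure fall or a vasopressor increase is one.

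Third, the power figures rest on assumed rates, shifts and cut-offs. This is correct, and they serve only as illustration.

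**Conclusion.** The point holds as an inconsistency in the primary safety outcome and a weak use of recorded data. Hemodynamics and SCPP are named as outcomes, but the listed outcome is an undefined event item with no stated analysis of MAP, SCPP, heart rate or vasopressor requirement. A corrected pressure fall can go uncounted; the article neither includes nor excludes it.

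The firm figure is the Fisher rejection region: 4 v 0, 5 v 0 or 5 v 1, given 5 per arm and participant-level scoring. The size of any masking cannot be derived from the article. This should be corrected before Phase 1 data are reviewed. It does not show that the trial will report a false absence of harm.

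**What to change.** 1. Reconcile the abstract, Table 1, Harms, Data collection methods and the stopping criteria, so that they name the same hemodynamic safety outcomes.
2. State whether the Table 1 item means the stopping criteria or something broader, and how a treated pressure change is classified. The clinical threshold stays with the investigators.
3. Add a safety row to Table 1, descriptive and not an extra primary test. It covers the in-session change in MAP, SCPP (where monitored) and heart rate from the last pre-session values, reported together with the change in vasopressor requirement and averaged per participant over sessions. Give it within participant in Phase 1, and as active v sham with a 95% CI in Phase 2.

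No dose, treatment threshold or stopping rule changes. The cost is a few more safety estimates to present. Pre-session values and SCPP would have to come from routine ICU monitoring, because the article does not state that they are recorded for the study. With 5 per arm the intervals will be wide, which suits the article's stated aim of estimating variability for later trials.

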### Analysis of patient-reported secondary outcome measures

At 6-month follow-up, patient-reported outcome measures will be: neuropathic pain as measured by the DN4, quality of life as measured by the NeuroQoL, and functional independence measured by the SCIM. For DN4 data, incidence (count data) and severity (ordinal) will be assessed by Chi square and independent samples *T* test, respectively. NeuroQoL and SCIM measures will also be analyzed using independent samples *T* test.

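### Table 1 assigns independent-sample tests (chi-square, Fisher) to within-subject MEP presence and to per-person muscle counts, and names no paired or participant-level method for them

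*Protocol article*

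**What the plan says.** In the Outcomes section, the MEP row of Table 1 describes "MEP present/elicited (binary measure) (within subject) # of muscles with elicitable MEP" and its analysis column reads "Data Type(s): Binary, Count Statistical Tests: Chi-Square, Fisher’s Exact Test". The EMG row includes "Change in number of muscles with EMG output" and its analysis column reads "Data Type(s): Continuous, Count Statistical Tests: Repeated Measures Analysis of Variance, Fisher’s Exact Test". Repeated-measures ANOVA fits the amplitude, which leaves Fisher for the muscle count.

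Data collection methods sets out the data structure. Ten surface electrodes cover five lower-limb muscles on each side. MEPs are assessed before and right after the first 60-minute session, and again at 7 days or discharge. The outcomes there are presence or absence of MEPs and "the number of muscles demonstrating elicitable responses".

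For DN4 pain at 6 months, the patient-reported outcomes analysis section says "incidence (count data) and severity (ordinal) will be assessed by Chi square and independent samples" t-tests respectively. Table 1 frames that comparison as "in tSCS vs. sham individuals (vs. historical TRACK-SCI participants").

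**The concern.** Chi-square and Fisher's exact test compare independent observations. A within-subject measure taken before and after stimulation is paired, and a change in a muscle count is a per-person difference. Neither is a two-by-two table of independent units.

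A 0–10 count can enter Fisher's test only if it is dichotomised or if muscles are pooled across people, and the plan does not say which. Two analysts following Table 1 could therefore produce very different p-values from the same data, some of them invalid. The trial is meant to supply variability and effect-size estimates for later studies, so a spurious or missed neurophysiological signal could be carried forward.

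**Working it through.** The plan states no error rate, power or sample size for these tests, so there is no figure to reproduce.

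**Inputs from the protocol article:** 5 active and 5 sham in Phase 2, plus 5 open-label in Phase 1 (Trial design); 10 muscles per person and three MEP assessments (Data collection methods); alpha 0.05 (Sample size), taken as two-sided.

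**Assumptions, not in the documents:** within-person correlation between muscles 0 to 0.7; muscle response rate 0.3 or 0.5; before/after correlation 0 to 0.7 at event rate 0.5.

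**1. Pairing, one binary value per participant.** With 5 pairs all changing the same way, exact McNemar gives its smallest two-sided p: 2 × (1/2)^5 = 0.0625. Treating the same data as two independent groups, 0/5 v 5/5:
- Fisher: 2 / C(10,5) = 2/252 = 0.0079.
- Chi-square without correction: 10 × (25)² / (5×5×5×5) = 10.0, p = 0.0016.

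For 0/5 to 4/5, Fisher gives 0.048, chi-square 0.0098 and McNemar 2 × (1/2)^4 = 0.125.

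The opposite also happens. For 4/15 to 10/15 with six gained and none lost, Fisher gives 0.066 and McNemar 2 × (1/2)^6 = 0.031. In simulation under no change (10 pairs, correlation 0.5), the unpaired tests reject in 0.5% (chi-square) and 0.08% (Fisher) of trials, so they are conservative there. Exact McNemar is conservative too at that size (0.05%), so the paired test is preferred because it fits the data, not because it gains power.

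**2. Muscle counts, if pooled as 50 v 50.** The design effect is 1 + (10 − 1) × correlation. Beta-binomial simulation with no true difference, 5 v 5 participants, 20,000 runs per setting, response rates 0.3 and 0.5:

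| Correlation (assumed) | Design effect | Fisher rejects at 5% |
|---|---|---|
| 0 | 1.00 | 3% |
| 0.05 | 1.45 | 8% |
| 0.1 | 1.90 | 12% |
| 0.3 | 3.70 | 28% |
| 0.5 | 5.50 | 37–38% |
| 0.7 | 7.30 | 46% |

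An extreme illustration is one active participant with all 10 muscles responding and nobody else. Pooled, 10/50 v 0/50 gives Fisher p = 0.0012. By participant, 1/5 v 0/5 gives p = 1.0.

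**3. Does another passage supply the right method?** The efficacy analysis section says RM-ANOVA will be run for each outcome measure, but its outcome list covers ISNCSCI scores, AIS grade and EMG amplitude, not MEPs or muscle counts, for which Table 1 names other tests. GEE, which could handle correlated counts, is named only for the proteomics.

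**4. DN4 incidence (minor).** At 5 v 5 with m events in total, the expected counts are m/2 and (10 − m)/2 in each arm, so at least two cells are always below 5. For 3/5 v 0/5:
- Chi-square: 10 × (3×5 − 2×0)² / (5×5×3×7) = 2250/525 = 4.29, p = 0.038.
- Fisher: 2 × C(5,3)/C(10,3) = 2 × 10/120 = 0.167.

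Enumerating all tables, the true type I error at 5 v 5 is at most 6.2% for uncorrected chi-square and 2.2% for Fisher. At 10 v 5, chi-square peaks at 5.0%.

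**The case against.** Several points on the other side are sound. Table 1 is described as an abbreviated analysis plan, so a fuller document may fix the unit of analysis. The efficacy analyses are declared exploratory, and these are secondary outcomes. The muscle outcome in Data collection methods reads naturally as one count per participant, not as pooled muscles.

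Three stronger readings are tempting, and the documents do not support them:
- **One responsive participant will, as written, yield a highly significant result.** That requires pooling muscles, which no section states. The table above is conditional on that choice and on assumed correlations.
- **Five per arm makes Fisher's p-value wrong.** It does not. With one value per person Fisher is exact and conservative. DN4 is neither paired nor clustered by muscle, and it is assigned chi-square. Its comparison may also be 10 v 5 (the Table 1 heading covers both phases) or against historical participants, and simple randomization does not guarantee 5 v 5.
- **Neurophysiology is the trial's main mechanistic readout.** The Objectives section gives mechanism to fluid biomarkers.

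What survives is that the tests Table 1 does name do not match data it describes as within subject or as change. A wrong test that is stated differs from a detail left to an analysis plan.

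**Conclusion.** The point holds for MEP presence and for the MEP and EMG muscle counts: independent-sample tests are specified for paired or multi-muscle data, and no suitable method is given elsewhere in the article. The error has no single direction. Ignoring pairing is often conservative, but with 5 pairs it can show p<0.05 where the exact paired test cannot. Pooling muscles, if done, is anti-conservative at every positive correlation examined. The pairing mismatch rests on the document's own labels; the size of the muscle effect rests on an unstated pooling choice and on assumed correlations.

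For DN4 incidence only a minor remark is justified: the chi-square approximation is poor at 5 v 5, but its real error rate stays near nominal. Because the outcomes are secondary and exploratory, this should be corrected but does not threaten the trial's primary conclusions.

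**What to change.** Revise the MEP and EMG rows of Table 1 to make the participant the unit of analysis.

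- **MEP presence:** exact McNemar test on participants for a named pair of time points, since McNemar takes two of the three assessments. Any between-arm comparison should use one value per participant, for which Fisher is suitable.
- **Number of muscles (MEP and EMG):** one count from 0 to 10 per participant at each assessment. Compare change between arms by exact permutation or exact Wilcoxon test, and within participants by signed-rank test.
- **Reporting:** give estimates with exact intervals. State that with 5 pairs the two-sided exact paired tests cannot fall below 0.0625, so a within-arm test in Phase 2 cannot reach 0.05, and at least six changes in one direction are needed (0.031). Say whether Phase 1 and Phase 2 active participants are combined for within-subject tests.
- **DN4 incidence (minor):** in Table 1 and the patient-reported outcomes section, replace chi-square with Fisher's or another exact test for the small tSCS v sham comparison, with an exact interval for the difference.

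The cost is wording only. Sample size, visits and data collection are unchanged.
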